| 4. The purpose of the study and its objectives; indication of the hypotheses, separated into primary and secondary hypotheses as well as the clinical parameters (primary and secondary endpoints), on the basis of which the hypotheses checked                                                                                                                                                                                                                                                                                     | The purpose of the study is the analysis and prediction of the hemodynamic result of interventions in patients with heart disease, particularly stenosis of the aortic isthmus, the pulmonary arteries and the aortic valve. To this end, image-based (MRI) modeling of the function
Hypothesis: The image-based modeling can predict hemodynamic parameters. Thus, for a diagnostic heart catheter examination could be replaced, and the hemodynamic effects before the intervention can be simulated and optimized, aiming towards optimized outcome.                                                                                                                                                                                                          |

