| 9. Substantial content and results of the previous studies/applications of research in the study of products to be tested                                                                                               | n.a.                                                                                                                                                                                                                                                                                                                                                                                                                                                                                    |
| 10. Description of the planned measures/methods of investigation and any deviations from the practice in the med. Usual measures/Studies (what is "routine", what is different in the study done?)                      | MR image data as well as the pressure values of heart catheter investigations are carried out in the framework of routine diagnostics will be used for the image-based modeling.
In patients consenting an MRI exam after an intervention (heart catheter or surgery) will be scheduled without the use of contrast agent. If after intervention (heart catheter or surgery) a clinical indication for an MRI control exists, any of these data is also be supplied to the analysis. |
| 11. Evaluation and consideration of the foreseeable risks and disadvantages of study participation against the expected benefits for the study participants and will in future be ill persons (benefit-risk assessment) | Disadvantages are not to be expected.                                                                                                                                                                                                                                                                                                                                                                                                                                                   |

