| A. Predictable therapeutic benefit for the study participants ( individual benefits for the individual patient)                                                                                                         | By modeling, participating patients could benefit from gain of knowledge for the future if re-interventions are necessary and ideally invasive diagnostic heart catheterization. In addition, heart catheter intervention/surgical procedures could be optimized in the future.                                                                                                                                                                                                         |
| As Foreseeable medical benefit for the future in the diseased persons ( group use)                                                                                                                                      | In future diseased patients diagnostic heart catheter examinations can ideally be replaced by MRI. In addition, the optimized results after heart catheter intervention/OP are expected.                                                                                                                                                                                                                                                                                                |
| C). Risks and burdens to the study participants (all in each list)                                                                                                                                               | The MRI study without contrast agent application is in compliance with the safety guidelines, and is without any proven risks.                                                                                                                                                                                                                                                                                                                                                          |

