| 
28. Procedure to protect the confidentiality of stored data, documents and any samples, presentations of pseudonym coding or anonymization of the data and samples of study participants (initials and date of birth as the encoding scheme are not allowed!)
 
 
- a description of the separation of medical records, study documentation and assignment of the personal data
 
- the access rights including access to participant identification lists during and after the study by management
 
- Detailed description of the procedure for the transmission, encryption, blocking and deletion (including an indication of any network structure and used server).
 
 | 
On inclusion each participant will be assigned a unique and randomly generated number (ID). For the evaluation of the study associated MRI results and heart catheter findings are only such data used in which the personal characteristics (Name, First Name, Sex, Date of birth, address) by this ID have been replaced.
 
The study documentation records are separate from the medical records in a locked cabinet. Access to the study documentation including the Participant Identification lists are available to the study leader and instructed employees, which can be study physicians and/or nurses.
 
The study-related data (image data, test results) will be stored on research servers within the DHZB (Intranet). The participant identification lists are stored on a separate computer to which only the study leader and IT staff have access.
                                                                                                                               |

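### Item 10 puts catheter pressures into the modeling that is meant to make the diagnostic catheter unnecessary, and nothing separates input pressures from comparison pressures

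*Protocol*

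**What the plan says.** Item 4 (purpose and hypotheses) calls the method "image-based (MRI) modeling of the function" and gives the hypothesis as "The image-based modeling can predict hemodynamic parameters". It then draws two consequences: "for a diagnostic heart catheter examination could be replaced, and the hemodynamic effects before the intervention can be simulated and optimized". So there are two aims: doing without the diagnostic catheter, and simulating an intervention before it is done.

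Item 11, under benefit to future patients, repeats the first aim: "In future diseased patients diagnostic heart catheter examinations can ideally be replaced by MRI". No catheter pressure is mentioned there as part of the replacement.

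Item 10 (planned measures) names the data. MR images and "pressure values of heart catheter investigations are carried out in the framework of routine diagnostics will be used for the image-based modeling". The two sources share one verb. After the intervention, item 10 plans imaging: "In patients consenting an MRI exam after an intervention (heart catheter or surgery) will be scheduled without the use of contrast agent".

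Item 28 (confidentiality) mentions catheter data once more: "For the evaluation of the study associated MRI results and heart catheter findings are only such data used". That sentence is about replacing identifiers with a study number.

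No item names a reference standard or an agreement measure, says which pressures enter the model, or holds any pressure back. Item 15 (biometric planning) is answered as not applicable because the study is a pilot.

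**The concern.** The protocol says the modeling might make the catheter dispensable, yet lists the catheter reading among the data for that modeling. Two separate problems follow if item 10 is carried out literally.

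The first is logical. A model that uses a patient's catheter pressure has required that patient to be catheterised. Its performance, good or bad, says nothing about a model working from MRI alone, so the replacement hypothesis would remain untested.

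The second is statistical and conditional. The protocol describes no other pressure measurement against which the model could be checked. If a pressure has set a boundary condition or calibrated the model, and the output is then compared with that same pressure, part of the agreement is built in. The reported error would be too small for an MRI-only model.

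Timing matters. Once modelers have built patient models with the pressures in hand, a blind MRI-only run on the same patients is hard to recover. A later analysis plan cannot restore it.

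**Working it through.** The protocol gives no agreement figure, SD, margin or power, so there is no stated number to reproduce. The check has two parts.

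**Part 1: the items side by side**

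| Item | Role of MRI | Role of catheter pressure |
|---|---|---|
| 4 | basis of the model | the examination that could be replaced |
| 11, future patients | what replaces the catheter | the examination to be replaced |
| 10 | used for the modeling | used for the modeling |
| 28 | evaluation data | evaluation data |

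Items 4 and 11 fit an MRI-driven model. Item 10, taken literally, describes an MRI-plus-catheter model. Item 28 adds that catheter findings are evaluation data, without saying in what role. Nothing in the four items stops the same pressure from being both input and comparator. The conclusion that such a model cannot support replacement needs no numbers.

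**Part 2: how built-in agreement would arise**

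This is an illustration; every value in it is assumed.

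- T is the true gradient, with SD sT = 15 mmHg.
- R = T + eR is the catheter reading, with error SD sR = 5 mmHg.
- M0 = T + eM is the MRI-only model, with error SD sM = 10 mmHg, independent of eR.
- M = (1 − w)·M0 + w·R is the reported model. Here w is the weight given to the same catheter value that later serves as comparator.

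The difference is M − R = (1 − w)(eM − eR), so:

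- limits of agreement = ±1.96 · (1 − w) · √(sM² + sR²)
- correlation = (sT² + w·sR²) / √(var R · var M), with var R = sT² + sR² and var M = sT² + (1 − w)²·sM² + w²·sR²

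At w = 0: 1.96 · √(100 + 25) = 21.9 mmHg, and r = 225/√(250 · 325) = 0.79. The other rows follow in the same way.

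| w | Apparent limits (mmHg) | Apparent r |
|---|---|---|
| 0 (comparison only) | ±21.9 | 0.79 |
| 0.25 | ±16.4 | 0.87 |
| 0.5 | ±11.0 | 0.94 |
| 0.75 | ±5.5 | 0.98 |
| 1 | ±0 | 1.00 |

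Varying sM from 5 to 15 mmHg:

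- At w = 0 the limits run from ±13.9 to ±31.0 (r from 0.90 to 0.67).
- At w = 0.5 they run from ±6.9 to ±15.5 (r from 0.98 to 0.89).

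Under this model the apparent limits are always (1 − w) times the MRI-only limits, whatever the SDs. MRI-only accuracy is the same in every row for a given sM. The protocol does not give w, so the inflation could be anything from none to complete.

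**The case against.** The strongest case on the other side has five parts.

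1. **The wording is loose.** The form is an awkward translation, and item 10 asks what is routine and what is added. The answer may simply list data sources, and used for the modeling can include validating the model. Read with items 4, 11 and 28, the study may already intend an MRI-driven model with catheter values for comparison. This stands as a possible reading. It is not the literal one, and the protocol allows both.

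2. **No reference standard or agreement analysis is stated.** This is correct. A reader might infer from item 10 that the reference standard is a model input and that agreement is therefore inflated. The documents do not support that as fact. The catheter as comparator is a reasonable inference from items 4 and 28, but item 28 concerns pseudonymisation. Inflation follows only if the compared quantity depends on the same pressure. If one pressure were a boundary condition and a different quantity were compared, the circularity would be smaller or absent.

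3. **Prediction is a separate aim.** To simulate an intervention, a pre-intervention pressure is a legitimate input and is not circular in itself, because the result comes later. This stands in full, and the protocol does not rank the two aims.

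4. **It is a pilot and replacement is a hope.** The wording is tentative, and no decision to omit catheterisation is tied to the study. That tempers the consequences. Yet replacement is part of the stated hypothesis, and a pilot that cannot bear on it loses one of its purposes.

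5. **A plan not shown may settle the details.** It may well define the agreement statistics, and their absence here is no fault. But which data go into the modeling is study conduct, and item 10 states it itself.

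**Conclusion.** The point holds in a conditional form. It is firm that item 10, read literally, conflicts with the MRI-only account in items 4 and 11, and that no item keeps input pressures apart from comparison pressures. It is also firm, without any assumption about size, that a model needing a patient's catheter pressure cannot support replacing the catheter.

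That agreement would be inflated is only possible. It requires the same pressure, or one that determines the compared quantity, to be both input and comparator. The documents do not say so, and the size cannot be computed from them. The millimetre figures above show the mechanism and are not an estimate for this study. The point does not extend to pre-intervention pressures used to predict the effect of an intervention.

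**What to change.** Amend item 10 before modeling starts.

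- State the role of each catheter pressure: model input, comparison value or not used, and whether it was taken before or after the intervention.
- For the replacement hypothesis, run the model on MRI and other non-invasive routine data only. Keep the modelers blind to catheter values until the outputs are fixed, and use the catheter pressures only for comparison.
- For predicting the effect of an intervention, pre-intervention catheter pressures may be inputs. Label that analysis catheter-informed and do not count it as evidence for replacement. Neither aim need be ranked above the other.

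The cost is a wording change and a rule on when pressures are released to the modelers. No extra patients or procedures are needed. The downside is that the reported agreement may look less favourable than that of a model informed by the catheter.

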| 12. Measures for risk control                                                                                                                                                                                           | n.a.                                                                                                                                                                                                                                                                                                                                                                                                                                                                                    |
| 13. Abort Criteria                                                                                                                                                                                                      | If patients or custody participation in the study revoked                                                                                                                                                                                                                                                                                                                                                                                                                               |
| 14. Number, age and sex of the persons concerned                                                                                                                                                                        | 20 patients with pulmonary stenosis, 40 patients with coarctation of the aorta, 60 patients with aortic valves disease, undergoing treatment. of different ages and different genders                                                                                                                                                                                                                                                                                                   |

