| 15. Biometric planning with specification of the statistical methodology, including the justification for the case number. Indication of the statistician/Statistics Erin                                               | n.a., because it is a pilot study.                                                                                                                                                                                                                                                                                                                                                                                                                                                      |

|                                                                                                                                                                                                                                                                       |                                                                                                                                                                                                                                                                  |
|-----------------------------------------------------------------------------------------------------------------------------------------------------------------------------------------------------------------------------------------------------------------------|------------------------------------------------------------------------------------------------------------------------------------------------------------------------------------------------------------------------------------------------------------------|
| 16.
A. Presentation and any explanation of the inclusion and exclusion criteria                                                                                                                                                                             | Inclusion criteria were any of the following diseases: pulmonary stenosis, aortic coarctation, aortic aortic valve disease in which MRI image data are available with the intervention                                                                           |

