| 18. If necessary: the reason for the inclusion and explanation of the therapeutic benefits for persons under age of 18 and/or the need for consent by a legal representative.                                                                                  | In congenital heart disease stenoses of the vessels (e.g., coarctation), and aortic valve disease (bicuspid aortic valve disease) are frequent congenital heart diseases, and often require interventions in children and in the course of growth are necessary. |
| 19. Relationship between study participants and study doctor/doctor (is the study doctor at the same time the doctor?)                                                                                                                                                | The study physician is also the treating physician.                                                                                                                                                                                                              |
| 20. Declaration on the inclusion of possible from the Sponsor dependent persons                                                                                                                                                                                       | n.a.                                                                                                                                                                                                                                                             |
| 21. Measures which allow a determination as to whether a study participants can be participating in several studies at the same time or before the expiry of a specified in the previous study period takes part
is the participation in several studies possible? | A simultaneous participation in another study is possible.                                                                                                                                                                                                       |

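### Item 10 sends scheduled and clinically indicated post-intervention MRIs to one analysis, so inclusion in the prediction analysis may depend in part on the outcome being predicted

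*Protocol*

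**What the plan says.** Protocol item 4 gives the aim: "The purpose of the study is the analysis and prediction of the hemodynamic result of interventions in patients with heart disease". The hypothesis in the same item is that "The image-based modeling can predict hemodynamic parameters". For the prediction part, post-intervention imaging therefore serves as the reference.

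Item 10 names two sources of that imaging:

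- A study scan: "In patients consenting an MRI exam after an intervention (heart catheter or surgery) will be scheduled without the use of contrast agent".
- A routine scan: if, after the intervention, "a clinical indication for an MRI control exists, any of these data is also be supplied to the analysis".

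Item 10 gives no time point for either scan, does not define the indication, and does not say that the sources are to be told apart. Item 16A admits patients with one of the three diseases "in which MRI image data are available with the intervention", and no item makes a post-intervention MRI a condition for all. Item 14 plans "20 patients with pulmonary stenosis, 40 patients with coarctation of the aorta, 60 patients with aortic valves disease, undergoing treatment". Item 15, on statistical methodology, answers "n.a., because it is a pilot study". Item 19 states: "The study physician is also the treating physician". Item 25 mentions an eCRF sheet without listing its fields.

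**The concern.** A participant who has the scheduled MRI enters the prediction analysis whatever the result. A participant who does not have it enters only if a clinical indication arises. It is plausible, though the protocol does not say so, that a control MRI after treatment of a stenosis or valve lesion is sometimes ordered because a residual or recurrent lesion is suspected. For that subgroup, entry would then depend on the hemodynamic result and, through it, on the gap between result and prediction. A model that is unbiased in all treated patients could appear to predict results that are too favourable.

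Two features add to this. Without a common time point, a planned control can be mixed with a scan made whenever a problem appears. And the study physician, who is also the treating physician, may order the indicated scan knowing the result.

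**Working it through.** **No plan figure to reproduce.** The protocol states no alpha, power, effect size, SD or accuracy threshold. The group sizes add to 20 + 40 + 60 = 120. All other inputs below are assumptions, chosen to show a range.

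**Set-up.** The outcome is y = p + e, where p is the prediction and e an error with mean 0 in the full population, so the model is unbiased. A correlation ρ between prediction and outcome of 0.5, 0.7 or 0.9 sets SD(e) = √(1/ρ² − 1) in units of SD(p). A share c (consent rate) has the scheduled MRI, independently of outcome. The probability of an indication follows logit = log(0.3/0.7) + log(OR) × z, where z is the standardised outcome (higher is worse). That means a 30% probability at the mean outcome and an odds ratio (OR) of 1, 2 or 4 per SD worse. A patient is included if scheduled or indicated. One million draws were used for each setting.

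**Formula.** Scheduled patients have mean error 0, so

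bias = (share of the analysed set entering by indication only) × (mean error in that share).

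Example at ρ = 0.5, OR 4, c = 50%: 0.26 × 0.581 = 0.151 (simulated 0.153). At c = 20%: 0.58 × 0.585 = 0.339 (simulated 0.341).

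**Bias in SDs of the prediction error (range over ρ = 0.9 to 0.5):**

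| Share with scheduled MRI | OR 1 | OR 2 | OR 4 |
|---|---|---|---|
| 100% | 0 | 0 | 0 |
| 80% | 0 | 0.014–0.029 | 0.023–0.048 |
| 50% | 0 | 0.046–0.093 | 0.075–0.153 |
| 20% | 0 | 0.105–0.211 | 0.169–0.341 |

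Zeros are to within simulation error. Among patients who enter by indication only, mean error is 0.19 to 0.38 SD at OR 2 and 0.29 to 0.59 SD at OR 4. The calibration slope hardly moves (0.97 to 1.01).

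**A harsher trigger, in mmHg.** Assume a predicted residual gradient N(10, 6), error SD 8, and an indicated MRI in every patient whose true residual exceeds 20.

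- The residual has SD √(36 + 64) = 10, so P(residual > 20) = 1 − Φ(1) = 0.159.
- Mean error given an indication = (64/10) × φ(1)/0.159 = 6.4 × 1.525 ≈ 9.8 mmHg.
- Pooled bias = (1 − c) × 0.159 × 9.8 / [c + (1 − c) × 0.159], which is about 1.9, 1.3 and 0.6 mmHg at c = 40%, 50% and 70%. Divided by 8, that is 0.24, 0.17 and 0.08 SD.
- The share of poor results rises from 16% to 0.159/0.495 = 32%, 0.159/0.579 = 27% and 0.159/0.748 = 21%.

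With the same 16% indication rate but a graded trigger (OR 2 to 4), the bias falls to 0.7–1.2, 0.5–0.8 and 0.2–0.4 mmHg. Even with the hard cutoff it is only 0.2 mmHg at 90% consent.

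**Against sampling error.** The 95% half-width of a mean error is 1.96/√n: 0.44, 0.31 and 0.25 SD at n = 20, 40 and 60, or about 3.5, 2.5 and 2.0 mmHg at SD 8. At n = 120 it is 0.18 SD. The largest bias, 0.34 SD, arises when only 48% of patients are included. The groups then hold about 10, 19 and 29 patients, with half-widths of about 0.63, 0.45 and 0.37 SD. Within a disease group the bias therefore stays below sampling error. Unlike sampling error, it does not shrink with more patients.

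**The case against.** Four points can be made for the plan.

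*The link between indication and poor result is inferred.* A control MRI can be ordinary follow-up, and item 23 says patients remain in continuous cardiologic care. This stands: with OR 1 the bias is zero at any consent rate. A reader might infer that indicated scans are over-selected for poor results, but the protocol does not say what triggers them.

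*Consent may mean consent to the study.* Item 16 requires informed consent for participation, and item 29 links additional investigations to study participation. On that reading every participant is scheduled for the MRI, and indicated scans only add data in patients who are already included. This also stands as a possible reading. It removes the inclusion bias, but not the question of which scan, at which time, counts as the result.

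*Supplying data to the analysis is not pooling.* The sentence names a data source. A statistical analysis plan, not shown here, could separate the sources. This stands in part. An analysis plan can only separate scans whose reason was recorded when they were made, and that is a matter of data collection.

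*A scheduled-only set may itself be selected.* If patients with poor results consent less often, restricting to scheduled scans does not give a representative sample. This stands, and is why the fix includes a comparison of patients with and without the scheduled scan.

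The dual role in item 19 might suggest that scans are ordered to suit the study. Nothing in the protocol supports that.

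**Conclusion.** The point holds in a limited form. Item 10 lets two differently selected sources of outcome data into one analysis, without a common time point or a requirement to record the reason for the scan. If some participants do not have the scheduled MRI, their inclusion may depend in part on the outcome.

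The bias in mean prediction error runs from zero to about 0.34 SD over the assumed range, with 0.05 to 0.15 SD at 50% consent and OR 2 to 4. It needs three conditions that the protocol does not settle: some participants without the scheduled MRI, indications that track the result, and an analysis that does not separate the sources.

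A reader might conclude that inclusion does depend on the outcome and that the prediction results would be invalid. The documents do not support that. The consent rate and the share of indicated-only scans are unknown, no mean-error endpoint is named, and the study is described as a pilot. Nor is the catheter-replacement part of the hypothesis shown to be affected, since it can be tested on the routine MRI and catheter pressures of item 10.

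Severity is moderate to low: a cheap improvement.

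**What to change.** In item 10:

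1. State that the main prediction analysis uses the scheduled post-intervention MRI, in one window that the investigators fix in advance, with consent to that scan sought at enrolment.
2. Record the reason and date of every post-intervention MRI in the eCRF named in item 25.
3. Analyse indicated-only MRIs separately or as a sensitivity analysis.
4. Compare pre-intervention characteristics of patients with and without the scheduled MRI, since a consent-based set may itself be selected.

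Under the assumptions above, steps 1 and 3 reduce the bias from this route to zero. Selective consent remains a separate matter, which step 4 makes visible. The cost is a wording change, two eCRF entries and a slightly smaller main prediction set. No data are discarded. The reason for the scan should be captured as scans are made, because it may not be reliably recoverable later.
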